## Abstract

**Background:**

Optimizing return to work (RTW) after knee arthroplasty (KA) is becoming increasingly important due to a growing incidence of KA and poor RTW outcomes after KA. We developed the Back At work After Surgery (BAAS) clinical pathway for optimized RTW after KA. Since the effectiveness and cost analysis of the BAAS clinical pathway are still unknown, analysis on effectiveness and costs of BAAS is imperative.

**Method:**

This protocol paper has been written in line with the standards of Standard Protocol Items: Recommendations for Interventional Trails. To assess the effectiveness and cost-effectiveness for RTW, we will perform a multicenter prospective cohort study with patients who decided to receive a total KA (TKA) or an unicompartmental KA (UKA). To evaluate the effectiveness of BAAS regarding RTW, a comparison to usual care will be made using individual patient data on RTW from prospectively performed cohort studies in the Netherlands.

**Discussion:**

One of the strengths of this study is that the feasibility for the BAAS clinical pathway was tested at first hand. Also, we will use validated questionnaires and functional tests to assess the patient’s recovery using robust outcomes. Moreover, the intervention was performed in two hospitals serving the targeted patient group and to reduce selection bias and improve generalizability. The limitations of this study protocol are that the lead author has an active role as a medical case manager (MCM) in one of the hospitals. Additionally, we will use the data from other prospective Dutch cohort studies to compare our findings regarding RTW to usual care. Since we will not perform an RCT, we will use propensity analysis to reduce the bias due to possible differences between these cohorts.

**Trail Registration:**

This study was retrospectively registered at clinicaltrails.gov (https://clinicaltrials.gov/ct2/show/NCT05690347, date of first registration: 19–01-2023).

**Supplementary Information:**

The online version contains supplementary material available at 10.1186/s12891-023-06203-5.

## Background

Optimizing return to work (RTW) after knee arthroplasty (KA) is becoming increasingly important due to the growing incidence of KA and poor RTW outcomes after arthroplasty. The incidence of KA is predicted to rise substantially in the coming decades in countries with established market economies [1–4]. The largest increase is expected among patients of working age [5]. For instance, in 2030 the United States of America will be the first country where the majority of patients getting KA are of working age, followed by Great Britain in 2035 [3, 4]. Although outcomes regarding pain relief and improved knee function after KA are satisfactory, RTW among patients getting KA is relatively low. Prospectively reported non-RTW rates are 33% within six months after KA and 13% within 12 months in the Netherlands [6]. Also, the economic burden of knee osteoarthritis in the Netherlands is high. The average annual cost for the Dutch workforce due to sick leave for knee osteoarthritis was 26.9 million euros between 2015 and 2017 [7]. Considering the increase in the demand from patients seeking KA, the low RTW outcomes after KA, and a high economic burden, care optimization for patients getting KA with a focus on RTW is essential.

A closer collaboration between professionals in medical care (e.g. orthopedic surgeon, physical therapist) and occupational care (e.g. occupational physician) for working-age patients with KA might improve their RTW probabilities after surgery [8]. From the patient perspective, an individual tailored, integrated (health care and work-directed), comprehensive (from pre-operative to RTW) clinical pathway should preferably include integrated and coordinated care from four domains: (i) rehabilitation (e.g. physical therapy); (ii) patient support (e.g. setting proper goals); (iii) occupational support (e.g. proper build-up modified work); and (iv) medical support (e.g. more personal guidance from the hospital) [9, 10]. Unfortunately, proven effective work-directed care is currently not available for patients receiving KA [11, 12].

Recently, an integrated clinical pathway called Back At work After Surgery (BAAS) was started, aiming to improve RTW after KA. BAAS was proven feasible in 2021 in practice (Additional file 1: Appendix I) [13]. The development of this care pathway was based on two pillars [14]. The first pillar was a timely combination of medical and occupational care, and the second pillar was enhancing patient participation during the clinical pathway. In this way, interdisciplinary communication was improved by making RTW an explicit outcome of the rehabilitation, which might accelerate both rehabilitation and RTW. The next step is to analyze the effectiveness and costs of the BAAS clinical pathway to RTW.

To the best of our knowledge, this is the first study on work-directed and patient-centered care after KA systematically involving health care experts other than an orthopedic surgeon and a physical therapist. Timely involvement of occupational care experts seems to be an important evidence-based prerequisite to ensure that the BAAS clinical pathway can be more effective on RTW after KA than usual care [6, 13, 15]. However, since the true effectiveness and costs or benefits of the BAAS clinical pathway are still unknown, analysis on effectiveness and economic evaluation of BAAS is expedient. Our hypotheses are that an integrated clinical pathway with a focus on RTW after KA is more effective on RTW than usual care, and has a positive economic evaluation.

This multicenter study has two aims. Firstly, to assess the effectiveness of the BAAS clinical pathway for RTW compared to usual care. Secondly, to evaluate the economics of the BAAS clinical pathway compared to usual care. This paper describes the study protocol for the multicenter study.

## Methods

### Study design

This protocol paper has been written in line with the standards of Standard Protocol Items: Recommendations for Interventional Trails (SPIRIT) [16]. We will perform a multicenter prospective cohort study with patients who have decided to be given a total KA (TKA) or a unicompartmental KA (UKA). To establish generalizability, the BAAS pathway will be performed in two high-volume KA hospitals in the Netherlands serving a representative population of working patients receiving KA. For the effectiveness of BAAS regarding RTW, the results of the study will be matched in pairs and compared to individual patient data on RTW by matched pairs from prospectively performed cohort studies in the Netherlands on care as usual, namely the Expect to Work cohort and the ACTIVE trial [17, 18]. For the economic evaluation, a comparison will be made with individual patient-level data using the care-as-usual group of the ACTIVE trial in the Netherlands [17]. The study has been approved by the Medical Ethical Committee of the Amsterdam UMC, location AMC (reference ID: W21_454 # 21.504) and the Medical Ethical Committees of the local hospitals Nij Smellinghe (NS, reference ID: 19,888) and Elizabeth Tweesteden Ziekenhuis (ETZ, reference ID: L1429.2021).

### Study setting

This study will take place in two hospitals in the Netherlands. The first is Nij Smellinghe (NS) hospital located in Drachten, in the northern part of the Netherlands. NS has approximately 320 clinical beds and three orthopedic surgeons who perform approximately 350 KAs a year. The second is the Elizabeth Tweesteden Ziekenhuis (ETZ), a larger regional hospital located in Tilburg, in the southern part of the Netherlands. ETZ has 940 beds and 6 orthopedic surgeons who perform approximately 700 KAs a year.

### Participants

#### Sample size

A minimal required sample size was calculated using R (version 3.6.3) with a power of 0.8 and a significance level of 0.05. The effect size was calculated with a mean difference of two weeks in comparison to a Dutch study on RTW after KA [15]. With a calculated minimal required sample size of 125 and an expected loss to follow-up of 20%, we intend to include 150 patients (75 in NS and 75 in ETZ).

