### Statistical methods

#### Effectiveness

The effect of the BAAS care pathway on time to RTW will be statistically tested using survival analysis and gamma regression analysis including bootstrapping using R (version 4.1.0). Missing data will be handled by multivariate imputation using the aforementioned prognostic factors if possible [46]. For the repeated measurements on the time to RTW and/or full RTW, a mixed model will be used to test and estimate the size of the BAAS effect controlling for the following potential prognostic factors of delayed RTW, namely UKA vs TKA, primary vs revision KA, gender, BMI, physical nature of the job, preoperative sick leave, and patient-reported work-relatedness of knee symptoms. Hazard ratios including 95% confidence intervals will be calculated for the intervention group and tested against both control groups. In the absence of an empirically derived MCID, a difference of two weeks will be considered clinically relevant for first day of RTW and one week for full RTW. For interpreting the magnitude of the standard mean difference (SMD), three groups are defined: (i) small (SMD = 0 – 0.2); (ii) medium (SMD = 0.2 – 0.5) and (iii) large (SMD = 0.5–1.0) [47]. Sensitivity analyses on RTW will be performed for the two hospitals. Analyses will be conducted using both univariate and multivariate analyses to assess the effect size of the BAAS care pathway with and without controlling for variables. Lastly, because this control group is not from the same cohort as the intervention group, we will use propensity analysis (matched pairs) to correct for other confounding factors [48]. Potential prognostic factors for delayed RTW like UKA vs TKA gender, BMI, physical nature of the job, preoperative sick leave and patient-reported work-relatedness of knee symptoms will be used for patient matching. Secondary outcomes will be plotted in time and will be tested on differences between the usual care cohorts and the intervention cohort.

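### The stated 80% power is not established for the planned comparison of BAAS patients with matched controls

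*Protocol article*

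**What the plan says.** The Sample size section takes a power of 0.8 and a significance level of 0.05, and bases the effect on one published study: "The effect size was calculated with a mean difference of two weeks in comparison to a Dutch study on RTW after KA [15"]. It then goes directly to recruitment: "With a calculated minimal required sample size of 125 and an expected loss to follow-up of 20%, we intend to include 150 patients", split as 75 at each hospital. Both hospitals deliver the BAAS pathway (Study design), so all 150 are BAAS patients.

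The analysis is of another kind. Study design says the BAAS results will be "matched in pairs and compared to individual patient data on RTW by matched pairs from prospectively performed cohort studies in the Netherlands", naming the Expect to Work cohort and the ACTIVE trial (references 17 and 18). Primary outcomes assigns the first to first day of return to work (RTW) and the ACTIVE comparison group to full RTW. Statistical methods, Effectiveness, adds propensity-matched pairs and states: "Hazard ratios including 95% confidence intervals will be calculated for the intervention group and tested against both control groups".

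**The concern.** The calculation is referenced to a study that supplies no controls, yields a single number, and turns that number into intervention patients only. The test is then run against other patients, whose own variability must be counted. Nothing in the section links 125 to a number of controls or matched pairs.

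The 0.8 is the only power statement in the article. The two-week difference behind it is also the difference that Effectiveness calls clinically relevant for first day of RTW. If power for the matched comparison is well below 0.8, a null result would say little about BAAS, yet readers would take it as coming from an adequately powered study.

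**Working it through.** **Inputs from the article.** Power 0.80, alpha 0.05, difference 2 weeks, n = 125, loss 20%, planned 150. Sidedness, SD, type of test, and whether 125 is per group or total are not printed. I assume two-sided testing and 1:1 matching. The multiplier is 1.960 + 0.842 = 2.802.

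**Step 1: can 125 be reproduced?** Not without an SD. Solving for the SD that gives 125 under each design:

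- One-sample: SD = 2 × √125 / 2.802 = 7.98 weeks (7.92 with the t distribution).
- Two-sample, 125 per group: SD = 2 × √(125/2) / 2.802 = 5.64 weeks.
- Two-sample, 125 in total: SD = 2 × √(62.5/2) / 2.802 = 3.99 weeks. This reading does not fit the text, because 125 is inflated directly to 150 BAAS recruits.

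**Step 2: how many patients remain?** 125 × 1.2 = 150, but 150 × 0.8 = 120. Retaining 125 after 20% loss needs 125/0.8 = 156.25, that is 157. The allowance covers loss to follow-up only, not BAAS patients for whom no match is found.

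**Step 3: power of the matched comparison.** For n pairs with within-pair correlation ρ, power = Φ(2 / [SD × √(2(1−ρ)/n)] − 1.960).

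One-sample origin, SD 7.98. At n = 125 and ρ = 0, the standard error is 7.98 × √(2/125) = 1.01, so power = Φ(1.98 − 1.96) = 0.51.

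| ρ | n = 120 | n = 125 |
|---|---|---|
| 0 | 0.492 | 0.508 |
| 0.1 | 0.534 | 0.551 |
| 0.2 | 0.583 | 0.601 |
| 0.3 | 0.641 | 0.658 |
| 0.5 | 0.784 | 0.800 |

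The t distribution gives 0.495 and 0.512 for the first row. The difference detectable with 80% power at ρ = 0 is 2.802 × 7.98 × √(2/n), which is 2.8 weeks at 125 pairs and 2.9 weeks at 120.

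Per-group origin, SD 5.64, ρ = 0:

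| Pairs | Power |
|---|---|
| 125 | 0.80 |
| 120 (150 less 20%) | 0.78 |
| 108 (120 less 10% unmatched) | 0.74 |
| 96 (120 less 20% unmatched) | 0.69 |

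The 10% and 20% unmatched are illustrations; the article gives no figure.

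**Step 4: two controls per BAAS patient.** Replace 2/n by 1/n + 1/(2n), with ρ = 0. With SD 7.98, power is 0.61 at n = 120 and 0.63 at n = 125. With SD 5.64, the standard error at n = 125 is 5.64 × √0.012 = 0.618, so power = Φ(3.24 − 1.96) = 0.90; at n = 120 it is 0.89.

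All these figures are for a difference in means. Power for the planned hazard ratios would need assumptions about the RTW distribution that the article does not give.

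**The case against.** A reader might infer that the true power is 50-60%, because one number, all BAAS, set against one published study, looks like a one-sample test. The article does not support that as a finding. It says the effect size was derived by comparison with reference 15, which may only mean that this study supplied the inputs for an ordinary two-group calculation. Because the controls already exist, the authors would naturally print only the number to recruit. On that reading, 125 BAAS patients with 125 matched controls have exactly the stated 80%.

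Two arguments for the one-sample reading do not settle it. An SD of 8 gives 125.6 in a one-sample formula, but a standardised effect of 0.50 in a two-group formula gives the same total. It is also tempting to rule out the smaller SDs from the Background statement: "Prospectively reported non-RTW rates are 33% within six months after KA and 13% within 12 months in the Netherlands". That figure comes from another cohort, which the Discussion says measured full RTW by questionnaire category, whereas reference 15 measured time to first RTW. The tail of one cannot fix the spread of the other.

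The matching factors are those the plan regards as prognostic, so some positive within-pair correlation is to be expected and would raise every 1:1 figure above that sets it to zero. A condensed article may also leave the SD and the test to the full protocol, so their absence is not in itself an error.

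These points defeat a claim of one known power value. They do not remove the mismatch between the comparison that was sized and the comparison that will be tested.

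**Conclusion.** The point holds in limited form: the stated 80% is not established for the matched comparison. On the one-sample reading power is about 50% with independent controls and 53-66% at within-pair correlations of 0.1-0.3; a correlation of 0.5 is needed for about 80%. On the per-group reading it is 80% only with 125 complete pairs, 78% with the 120 expected to remain, and 69-74% if 10-20% of those find no match. On either reading that counts 125 as BAAS patients, 80% is therefore not secured before any gain from within-pair correlation. The figures assume two-sided testing at 0.05, 1:1 matching and back-solved SDs. Which reading applies cannot be decided from the article.

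**What to change.** Keep enrolment at 150. Replace the calculation with one for the comparison of BAAS patients with matched controls. State the SD and test behind the authors' calculation, the expected retained number (120, not 125), and the expected number of matched pairs in each control cohort. Then restate the resulting power or the detectable difference.

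State a power of roughly 50-60% (within-pair correlation 0 to 0.2), or 80% power for about 2.8-2.9 weeks with independent controls, only if the authors' calculation is confirmed as one-sample with an SD of about 8 weeks.

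Where a cohort holds enough controls, match two per BAAS patient. At 120-125 BAAS patients this gives about 61-63% on the one-sample reading and 89-90% on the per-group reading, ignoring within-pair correlation.

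The cost is one recalculated paragraph and possibly a less favourable stated power. No new patients are needed. The second control uses existing data, at the price of slightly looser matches and a change from the planned pairs.

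### Minor arithmetic error: enrolling 150 with the plan's own 20% loss leaves 120 patients, below its stated minimum of 125

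*Protocol article*

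**What the plan says.** The protocol article, under Participants, Sample size, reports a calculation in R "with a power of 0.8 and a significance level of 0.05". On the effect it says: "The effect size was calculated with a mean difference of two weeks in comparison to a Dutch study on RTW after KA". It gives no standard deviation, standardised effect, test or sidedness. It then links three figures in one sentence: "With a calculated minimal required sample size of 125 and an expected loss to follow-up of 20%, we intend to include 150 patients", split as 75 in each of the two hospitals.

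All 150 are patients in the BAAS pathway. Under Study design and Primary outcomes, the usual-care comparators come from two other Dutch cohorts and are not part of the 150. No other section gives a different enrolment target, a different loss rate, or a rule by which lost patients still count towards the 125.

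**The concern.** A target inflated for attrition should leave at least the required number once the assumed loss has occurred. Here it does not: the target, the loss rate and the minimum are in the same sentence, and the first two together give a number below the third. Readers use the sample size statement to judge how informative a null result would be. As written, it implies that 0.8 power is protected against 20% loss, and the stated figures do not support that.

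**Working it through.** **Inputs, all from the Sample size section:** required number 125; power 0.8; significance level 0.05 (taken as two-sided, since sidedness is not stated; one-sided also shown); difference two weeks; loss 20%; target 150.

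**1. Reproducing the plan's figure.**
- Multiplying by one plus the loss rate: 125 × (1 + 0.20) = 150. This matches exactly.
- Dividing by one minus the loss rate: 125 / (1 − 0.20) = 156.25, rounded up to 157. This does not match.

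**2. What 150 delivers.**
- Retained at 20% loss: 150 × 0.8 = 120, which is 5 below 125 (5 / 125 = 4%).
- Largest loss that still leaves 125: 1 − 125/150 = 16.7%.

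**3. What would deliver 125.**
- 156 × 0.8 = 124.8, just short.
- 157 × 0.8 = 125.6, enough.
- With an equal split, 158 (79 per hospital): 158 × 0.8 = 126.4.

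**4. Effect on power.** The 125 cannot be recomputed, because no standard deviation is given. I therefore take it as the number of BAAS patients that gives exactly 0.80, and rescale. By the normal approximation, 0.80 power at two-sided 0.05 means a noncentrality of 1.960 + 0.842 = 2.802.

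- *Both sides of the comparison shrink together (pairs, or one sample):* 2.802 × √(120/125) = 2.745. Power = Φ(2.745 − 1.960) = Φ(0.785) = 0.784. At one-sided 0.05 the same step gives 0.786.
- *Comparator size fixed at m:* multiply 2.802 by √[(1/125 + 1/m) / (1/120 + 1/m)]. The documents do not give m, so these values are assumptions:

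| Assumed m | Two-sided power with 120 BAAS patients |
|---|---|
| 125 | 0.792 |
| 250 | 0.789 |
| 500 | 0.787 |

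Nominal power is therefore about 0.78 to 0.79, a fall of about 1 to 1.6 percentage points.

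**5. What standard deviation the 125 implies.** For a two-week difference, 125 implies an SD of about 5.6 weeks if it is a per-group number, and about 8.0 weeks if it is one-sample or paired. The text does not say which was used. The rescaling in step 4 does not need the SD.

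**The case against.** The strongest defence is that lost patients are not wholly lost. The Effectiveness section plans survival analysis with hazard ratios, in which someone lost before returning to work would ordinarily be censored and not dropped. It also plans imputation where feasible. Full return to work ends the pathway and its follow-up measurements, so a patient who leaves after that point has already supplied the primary outcome. This stands in part: 0.78 to 0.79 is a rescaled mean-difference calculation, not the power of the planned analysis. It does not rescue the sentence. The Sample size section takes no credit for censoring or imputation, and by inflating for loss it treats those patients as gone.

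It is also fair to say that five patients and a point or two of power change no design choice or analysis. That stands, and it sets the grade.

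Two stronger readings are tempting, and the documents do not support either.

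- *That power falls to 78% whatever the 125 refers to.* If 125 were a total over two groups, only about 63 BAAS patients would be needed, and 120 is nearly double that. The implied standardised difference would be 2.802 / √(62.5/2) = 0.501. With 120 per group, power would be Φ(0.501 × √60 − 1.960) = Φ(1.92), about 0.97, so there would be no shortfall in power. The article inflates 125 directly to a BAAS-only target, which makes the per-group or one-sample reading the natural one. The power figure holds only under that reading.
- *That matching cuts the sample much further.* The Effectiveness section says "we will use propensity analysis (matched pairs) to correct for other confounding factors", so a reader might infer that unmatched patients bring the number well below 120. The article gives no comparator cohort sizes, matching ratio or caliper, so no match rate can be derived, and with large pools the loss could be close to nil. Covariate-adjusted models are planned as well, so it is not clear that unmatched patients leave every analysis. An allowance for match failure is detail that an article may leave to the full protocol or analysis plan.

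**Conclusion.** The error is real and minor. The required 125 was multiplied by 1.2 when it should have been divided by 0.8, so the target is 7 short of the 157 needed (8 short of 158 with equal sites). At the plan's own 20% loss, 120 remain against a stated minimum of 125. This part needs no assumption beyond the three printed figures.

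The power figure of about 0.78 to 0.79, against the stated 0.8, is conditional. It assumes that 125 is a number of BAAS patients (per-group, or one-sample or paired) giving exactly 0.80, and it ignores any information recovered by censoring or imputation. The study is not threatened; the sentence describing its size is wrong.

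**What to change.** Correct the sentence in the Sample size section in one of these ways:

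- State that 157 patients are required at 20% loss, or 158 with an equal split (79 per hospital).
- Keep 150 and state that it allows for a loss of at most 16.7%, if that is a loss rate the team can defend.
- Keep 150 and 20%, and state that this yields 120 patients and a nominal power of about 0.78 for the two-week difference. The team can take the exact value from its own R calculation at 120.

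The first option costs 7 or 8 more patients. The other two cost one reworded sentence and a slightly less favourable statement. No change to the analysis is needed.
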